# Perilla Oil and *Bifidobacterium* for Alleviating Fear of Cancer Recurrence in Breast Cancer Survivors: Study Protocol for a Three-Arm Phase II Randomized Controlled Study (POB Study)

**DOI:** 10.3390/mps4030046

**Published:** 2021-07-06

**Keywords:** fear of cancer recurrence, breast cancer, microbiome, probiotics, omega-3 fatty acids

## Abstract

The fear of cancer recurrence (FCR) is the most common and most severe unmet need among cancer survivors. Safe treatments for the FCR that are easily disseminated are greatly needed. Our primary aim is a preliminary evaluation of the efficacy and effect size of perilla oil, which is rich in omega-3 fatty acids, and *Bifidobacterium*, a probiotic, on FCR in breast cancer survivors after the completion of chemotherapy. This study has been planned as an exploratory clinical study (phase II) and will be conducted as a three-arm, 12-week parallel group, masked-rater randomized controlled trial. Fifteen participants will be randomized with 1:1:1 allocation to receive *Bifidobacterium* plus perilla oil, *Bifidobacterium* alone, or no intervention (control). Interventions will end within 12 weeks after the random allocation of each participant. The participants will be outpatients with invasive breast cancer aged 20 years or older whose chemotherapy was completed at least 6 months before registration; hormone therapy may be ongoing. The primary outcome will be severity of FCR at 12 weeks assessed by masked raters using the 4-item Concerns about Recurrence Scale concerning overall fear of recurrence. The study protocol for the current study is registered in the Japan Registry of Clinical Trials (jRCTs031200029).

## 1. Introduction

Among various types of psychological distress experienced by cancer survivors, the fear of cancer recurrence (FCR) is the most common and the most severe problem for which adequate support is often not available [1]. Longitudinal studies have shown that FCR can persist for years after finishing initial treatment, with more than half of cancer survivors experiencing moderately severe FCR and 7% experiencing extremely severe FCR [1]. Additionally, FCR is associated with after-hour visits, reduced quality of life, and reduced social functioning [1], suggesting the need for appropriate management. With the exception of extremely severe FCR, for which pharmacological and/or psychiatric therapies are implemented in line with current treatment practices for anxiety disorder, FCR is generally considered to be an extension of normal psychology and was reported to be the most frequently endorsed unmet need at the end of initial treatment and 6 months post-treatment in a multicenter study conducted in the United Kingdom [2]. A Japanese study of 408 breast cancer survivors also reported that 63% sought FCR-related care during treatment [3]. There is an ongoing need, therefore, for safe treatments for FCR that can be easily disseminated and that can offer cancer survivors a sense of security.

In previous work, psychological models were used to develop psychological therapies for FCR [4,5,6,7,8]. Additionally, it has also been suggested that there is an association between FCR and various biological risk factors, such as the presence and severity of physical symptoms and a history of chemical or radiation therapies [9]. FCR is a phenomenon in which reminders of cancer trigger the negative interpretation and recollection of fear memory, [4] and the degree of FCR is strongly related to intrusive memories as a symptom of post-traumatic stress disorder (PTSD) [10]. The pathology of PTSD is explained as the abnormal processing of fear memory, such as the enhancement of trauma-related fear memory consolidation [11] and the impairment of fear memory extinction [12]. This suggests that the dysregulation of fear memories is involved in the underlying cause of FCR.

Extensive studies investigating the regulation of fear memories have revealed that n-3 polyunsaturated fatty acids (PUFAs) [13,14,15] and gut microbiota play important roles in the brain functions related to fear memory regulation [16,17]. Our recent review suggested that n-3 PUFAs and the modulation of the microbiota–gut–brain axis improve dysfunctional fear memory processing via immunomodulation/anti-inflammation, increased levels of the brain-derived neurotrophic factor, upregulated adult neurogenesis, and modulated signal transduction [1]. Based on this, we hypothesized that an association exists among FCR, omega-3 PUFAs, and intestinal flora, and we conducted an observational study in 130 breast cancer survivors. We found lower FCR in those with higher blood levels of alpha-linolenic acid (ALA; an omega-3 PUFA found in perilla oil, linseed oil, and walnuts), and the association was independent of other psychiatric symptoms such as depressive symptoms [18]. We also found that FCR showed a positive correlation with the burden of Bacteroides, a proinflammatory bacterial species, and a negative correlation with the abundance of Firmicutes bacteria, which mainly produce butyric acid, a short-chain FA involved in the maintenance of the intestinal environment by improving intestinal barrier function. There was also a negative correlation with the diversity of the overall intestinal bacteria and a particularly strong correlation with the intestinal environment in patients after they had completed chemotherapy [19]. Based on these observations, we conceptualized the present study in which we will examine the effectiveness of nutritional intervention for cancer survivors with FCR.

Probiotics are live microorganisms that confer health benefit on the host when administered in adequate amounts (FAO/WHO Joint Working Group, 2001). Numerous studies have reported improved symptoms in patients with psychiatric disorders following probiotic interventions [20,21,22,23,24,25], and there is growing evidence of an interaction between omega-3 PUFAs and gut microbiota [26,27,28,29]. Diets rich in fish oil, which includes omega-3 PUFAs, increase *Bifidobacterium* levels and decrease Bacteroid levels compared to a diet rich in corn and beef fat [30]. Fat-1 transgenic mice engineered with the *Caenorhabditis elegans* Fat-1 gene can produce omega-3 PUFAs from Omega-6 PUFAs in their organs and tissues. The Fat-1 transgenic mice showed more production and secretion of intestinal alkaline phosphatase (IAP) than mice fed omega-6 PUFAs; the IAP decreased LPS production and gut permeability and suppressed endotoxemia and inflammation [31]. However, no studies have examined the effects of the combination of probiotics and omega-3 PUFAs to date.

This pilot study primarily aims to evaluate the efficacy and effect size of taking perilla oil rich in omega-3 PUFAs and *Bifidobacterium* as a probiotic on FCR in breast cancer survivors after they have completed chemotherapy. We believe the preliminary results will help to guide future full-scale confirmatory trials on their effects. Given the growing interest in the interaction between omega-3 PUFAs and intestinal flora, this study will also explore the optimal dosing regimen (*Bifidobacterium* alone vs. *Bifidobacterium* plus perilla oil).

## 2. Methods and Analysis

### 2.1. Study Design

This study has been planned as an exploratory clinical study (phase 2) and will be conducted as a three-arm, 12-week parallel group, masked-rater randomized controlled trial (RCT). The study is registered in the Japan Registry of Clinical Trials (jRCT; Trial ID jRCTs031200029). Participants will be randomized with 1:1:1 allocation to receive Bifidobacterium plus perilla oil, Bifidobacterium alone, or no intervention (control). A total of 15 participants will be allocated to each arm. These interventions will end within 12 weeks of the registration of each participant. The primary outcome will be FCR severity at 12 weeks as assessed by masked raters using the 4-item Concerns about Recurrence Scale (CARS) that asks about overall fear of recurrence.

### 2.2. Inclusion Criteria

Aged 20 years or older at the time of providing informed consent;Outpatient at the National Center of Neurology and Psychiatry hospital or the National Hospital Organization Tokyo Medical Center;Histologically or cytologically confirmed invasive breast cancer without cancer recurrence. The criteria is limited to invasive breast cancers because they are more likely to recur than non-invasive breast cancers and tend to be associated with a higher level of (more severe) FCR;Chemotherapy completed at least 6 months before registration. Hormone therapy may be ongoing. Patients who have only just completed chemotherapy will not be included because their diets tend to change due to stomatitis, and their gut environment can be unstable due to acute intestinal inflammation from the chemotherapy;At least a moderate level of fear (scoring ≥ 3 points) for the item of intensity of fear on the CARS, as previously reported by studies using the CARS [32,33];Recognition of cancer diagnosis. This criterion is set because a small number of people do not recognize themselves as having cancer, but the patients in the present study must recognize themselves as cancer survivors.

### 2.4. Participant Timeline and Recruitment

Patients will be recruited at the National Center for Neurology and Psychiatry (NCNP) hospital and National Hospital Organization (NHO) Tokyo Medical Center in Tokyo, Japan. Posters with study information will be displayed on the walls of the outpatient waiting room in both hospitals. Eligible patients will be screened through their medical records by their physician-in-charge. After the screening, all patients who meet the eligibility criteria will be approached by the research team in order to confirm the criteria. Those who satisfy all inclusion criteria and none of the exclusion criteria will receive a brief explanation of the study from the physician-in-charge. The clinical research coordinator (CRC) will provide sufficient written and verbal explanations and obtain written informed consent from the participants. Participants will then undergo baseline assessments. Figure 1 shows the flow of participants through the study.

### 2.5. Randomization and Masking

After completing the baseline assessment, participants will be randomly assigned at a of 1:1:1 allocation ratio to one of the three groups: the Bifidobacterium plus perilla oil group, the Bifidobacterium group, or the control group. Within the Hope eACReSS electronic data capture system (EDC) system, made available by the University Hospital Clinical Trail Alliance (http://plaza.umin.ac.jp/~UHCTA/edc.html, accessed on 5 July 2021), randomization will be performed using a minimization method and will be balanced using the following two factors: stratification age (<65 years, ≥65 years) and duration from diagnosis (<5 years, ≥5 years).

The primary outcome will be evaluated by the CRC and masked raters. At baseline, the CRC will evaluate the outcome before allocation. At 12 weeks, raters masked to all information regarding the allocation of this study will evaluate this outcome over the phone. The primary investigator (RO) will hold a workshop on the primary outcome evaluation for the CRC and masked raters using simulated recordings to confirm the evaluation method and will assess the inter-rater reliability for score evaluation. The primary outcome, FCR, is a subjective concept and result, and the CARS used in the evaluation is a self-reported scale, but in order to standardize the conditions of the responses, a masked rater will read the questionnaire aloud and will spend 5 min conducting the evaluation. This procedure is based on previous studies in which the primary outcome was a self-reported measure evaluated by masked raters [34,35].

### 2.6. Intervention Groups

In this three-arm RCT, two regimens of nutritional intervention, Bifidobacterium plus perilla oil and Bifidobacterium alone, will be compared to the control group. These two interventions will be completed within 12 weeks of the random allocation of the interventions. We have chosen perilla oil, which is rich in ALA, as an omega-3 supplement based on our observational and other studies. Consumption of a diet rich in ALA facilitates the inhibitory learning of original fear memories more than a diet rich in linolenic acids, one of the n-6 PUFAs, in rats [36]. An ALA-rich chocolate milkshake was recently found to facilitate the inhibitory learning of original fear memories in healthy individuals [37].

Participants in the Bifidobacterium plus perilla oil group will be asked to take 2 capsules (10 billion Bifidobacterium bacteria per capsule) and 1 sachet containing 3 g perilla oil (1.8 g ALA) daily with meals. Perilla oil may be mixed with soup or poured over salad or yogurt. Participants in the Bifidobacterium group will be asked to take 2 capsules (10 billion Bifidobacterium bacteria per capsule) with breakfast. Although there will be no restriction on concomitant drugs/treatments/procedures, information regarding concomitant drugs/therapies during the study will be collected as study data.

To enhance treatment adherence, participants will be contacted by telephone or email at 0, 4, 8, and 12 weeks of the study period. Participants will be informed that if they forget to take a capsule or sachet, they can take a 2-day dose at one time. They will be instructed not to chew the Bifidobacterium capsules. Participants in the intervention groups will be asked to report the number of weeks (0–12) that they have been taking their capsules and sachets during the 12 weeks and the reasons why they did not take them if they took ≤7 (i.e., compliance rate <60%).

### 2.7. Criteria for Discontinuing Allocated Interventions

The intervention protocol will be discontinued for any of the following reasons: (1) drop-out due to withdrawal of consent or declining to participate; (2) severe side effects (e.g., significant diarrhea); (3) sudden worsening of the participant’s condition after enrolment; (4) loss of contact with the participant; (5) the Principal Investigator and co-researchers determine that the mental and physical burden of the study on the participant is too much to continue the research(e.g., when life events or complications prevent the patient from consuming test foods, answering questionnaires, or submitting stool samples); and (6) deviation from the research protocol, such as when the selection criteria and exclusion criteria are found to be violated after taking the test capsules and sachets. 

### 2.8. Control Group

There will be no placebo capsule or sachet in this phase II trial. The reasons for this are detailed in Section 4. Participants in the control group will not receive any intervention during the study period. Although there will be no restriction on concomitant drugs/treatments/procedures, information regarding concomitant drugs/therapies used during the study will be collected as study data. Whenever inquiries are received from participants, the necessary information will be provided to them.

### 2.9. Data Collection Methods

The following information will be collected at the baseline assessment: age, sex, marital status, cancer stage, surgical history, history of radiation therapy, work status, family status, medication history (mental illness, other disease, antibiotic use, psychotropic drugs), body height/weight, and diet assessed using the Food Frequency Questionnaire (FFQ) [38,39]. For baseline characteristics, information will be collected from medical records as well as from the individual participants through questionnaires and interviews. We will also assess blood fatty acids at baseline with a custom test kit (Xerion Pharmaceuticals, Victoria, Australia) using dried blood spot testing as described previously [19]. All participants will receive a gift voucher for 2000 JPY (approximately 18 USD) for their participation after each assessment. An overview of the schedule for the assessments is shown in Table 1.

### 2.10. Primary Outcome Measures

The primary outcome will be FCR severity at 12 weeks as assessed by the masked raters using the 4-item CARS. The CARS comprises 30 questions [33] of which 4 concern overall fear of recurrence; the remaining 26 questions measure worries associated with recurrence under specific circumstances such as “worries about female sexuality” and “worries about future treatment”. These 26 questions will not be asked in this study. The 4 questions regarding overall fear of recurrence address the frequency, potential for upset, consistency, and intensity of fear. Each question is scored from 1 (no fear) to 6 (intense/frequent fear), giving an average score of 1 to 6, with higher scores indicating greater fear of recurrence. The validity of the Japanese version has been confirmed [40]. Participants who score ≥3 on overall fear of CARS will be categorized as having a moderate or high level of FCR [32,33].

### 2.11. Secondary Outcome Measures

Depressive symptoms will be assessed using the Japanese version of the Patient Health Questionnaire-9 (PHQ-9) [41]. The PHQ-9 is a self-rated questionnaire and focuses on 9 items regarding DSM-5 defined major depression in a structured diagnostic interview called the Primary Care Evaluation of Mental Disorders. Focusing on the preceding 2 weeks, each question is scored from 0 to 3, giving a total score of 0 to 27, where a lower the score was associated with a less depressed mood.

Irritable bowel syndrome (IBS) will be assessed using the Japanese version of the IBS severity index (IBS-SI) [42]. Total scores range from 0 to 500, summed from four subjective aspects; abdominal pain, abdominal distension, bowel movement, and quality of life. IBS is graded as mild (75–174), moderate (175–299), or severe (300–500) based on clinical observations of IBS patients [43].

Gut microbiota will be assessed using the participants’ fecal samples, which will be collected using a custom test kit and analyzed using meta-16S rRNA analysis as described previously [19].

### 2.12. Harm

Adverse reactions (ARs) will be collated as secondary outcomes. At 12 weeks after random allocation, we will specifically ask if participants have had any of the following ARs: headache, nausea, diarrhea, loose stool, and burping (if any, we will also ask about the time of onset, severity, subjective severity, need for treatment, and prognosis). The ARs of the participants in the intervention group will be monitored over the telephone by the CRC at 4 and 8 weeks after entry into the study. This step is based on previous studies reporting an 18% increased risk of ARs with omega 3 supplements compared to a placebo. The most common ARs were gastrointestinal and included nausea, diarrhea, and other minor gastrointestinal disturbances [44]. Clinical trials using Bifidobacterium have been conducted with only small sample sizes, and the ARs remain unclear.

An Efficacy and Safety Committee will be established, comprising an independent chair and at least two independent members. In the event of a serious illness for which a causal relationship to the intervention cannot be ruled out, this Committee will convene. If three serious illnesses for which a causal relationship to the intervention cannot be ruled out occur, the study will be stopped immediately without waiting for review by the Committee. The treatment of and care for ARs in patients enrolled in the study are covered by their medical insurance.

Participants who experience a substantial worsening of FCR or depressive symptoms during the study period will be promptly referred to a psychiatrist in collaboration with their physician. All of the test foods used in this study are commercially available and are well-established dietary products. Therefore, this study will not be covered by clinical research insurance. In the unlikely event that a research subject suffers health problems as a result of participation in this study, appropriate measures will be taken to provide the necessary treatment, including examination and treatment, within the research subject’s insurance coverage.

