***Assessment***					
Baseline characteristics of participants	CRC		×		
Blood fatty acid test	CRC		×		
Interstitial flora	CRC		×		×
CARS assessed via interview	CRC/masked rater		×(CRC)		×(masked raters)
PHQ-9	PRO questionnaires		×		×
IBS-SI	PRO questionnaires		×		×
Information about allocated groups	CRC			×	
Adverse reactions	CRC/PRO questionnaires				×
				← As needed throughout protocol →	

^1^ Baseline assessment and random allocation for completion within 3 weeks after registration in this study. ^2^ Outcome assessment will be conducted at 12 weeks from random allocation (allowing for a subsequent 14 days).

**Table 2 mps-04-00046-t002:** Data sharing policy for this study. Abbreviation: IPD, individual participant data.

Data Sharing Policy	
Is IPD available?	Yes
What types of data will be shared?	All anonymized IPD reported in the paper (body text, tables, and figures)
Are there any other documents available?	Protocol paper
How long will the data be available for?	For 5 years after publication of the paper
Who will use the data?	Researchers who have presented plans with appropriate methodologies
What types of analysis will this be used for?	For meta-analyses using IPD
How can the data be accessed?	Interested researchers should send a request for data sharing, along with a synopsis of the secondary analysis plan, to the Principal Investigator (RO) by email ([contact]). The study administrative office will examine the request and, if approved, send a letter of approval for data sharing to the requesting researcher.

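### The only adverse-reaction enquiry described for all three arms names five symptoms and no open question, so unlisted reactions may be recorded unevenly between arms

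*Protocol article*

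**What the plan says.** Section 2.12 of the protocol article gives ARs a formal role: "Adverse reactions (ARs) will be collated as secondary outcomes". It then states the week-12 enquiry: "we will specifically ask if participants have had any of the following ARs: headache, nausea, diarrhea, loose stool, and burping". A parenthesis in that sentence adds follow-up on onset, severity, need for treatment and prognosis.

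The next sentence describes a second route: "The ARs of the participants in the intervention group will be monitored over the telephone by the CRC at 4 and 8 weeks after entry". Its rationale is evidence on the oil component: "This step is based on previous studies reporting an 18% increased risk of ARs with omega 3 supplements compared to a placebo". On the component that both active arms receive, the section says: "Clinical trials using Bifidobacterium have been conducted with only small sample sizes, and the ARs remain unclear".

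Table 1 gives the source of the AR data as "CRC/PRO questionnaires" and marks them at the outcome assessment. Directly below that row stands "As needed throughout protocol".

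Section 2.14 plans relative risks for dichotomous outcomes, naming ARs, with chi-squared and Fisher's exact tests. It includes a comparison of the two active arms combined (n = 30) with control (n = 15).

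**The concern.** A list of named symptoms measures those symptoms comparably, but it is a poor instrument for reactions that nobody has yet characterised. The section says that this is the position for Bifidobacterium. The AR evidence it cites concerns omega-3 supplements.

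The second difficulty is asymmetry. A between-arm comparison of harms is fair only if events are looked for in the same way in each arm. Here the less restricted enquiry, the telephone calls, is described for the treated participants alone.

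At stake is a declared secondary outcome in a trial meant to inform a phase III study. Section 4 offers fewer adverse effects than psychotropic drugs as a reason why the intervention should be acceptable. Harms data that support such a statement should be able to show something unexpected, and show it equally in all arms.

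**Working it through.** No figure in the plan bears on this point, so there is none to reproduce. The check is a comparison of the described routes by which a reaction outside the five symptoms could be recorded, followed by a short illustration.

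**Routes for an unlisted, non-serious reaction**

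| Route (source) | Active arms | Control arm | Limits |
|---|---|---|---|
| Week-12 AR question (2.12) | Yes | Yes | Five named symptoms; no open item described |
| Coordinator's AR calls, weeks 4 and 8 (2.12) | Yes | Not described | No stated symptom list; last call at week 8 |
| As-needed entry (Table 1) | Not specified by arm | Not specified by arm | No scheduled enquiry; table layout is broken in the text at hand |
| IBS-SI, baseline and week 12 (2.11, Table 1) | Yes | Yes | Covers "abdominal pain, abdominal distension, bowel movement, and quality of life" as a symptom score, not as an AR record |

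Section 2.6 also mentions contacts at weeks 0, 4, 8 and 12. They are described under the intervention groups and for adherence, not as AR enquiries.

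Two gaps follow.

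1. In the control arm no active enquiry about unlisted reactions is described at any time.
2. In the active arms none is described after the week-8 call. That leaves 12 − 8 = 4 of the 12 weeks. With the 14-day allowance for the outcome assessment (Table 1, footnote 2) it can reach 6 weeks. Both figures take study entry as the date of allocation.

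**What this does to the planned relative risk**

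If the comparison uses only the week-12 answers, it is symmetric but covers five symptoms. If it also uses events from the calls, ascertainment differs by arm.

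To illustrate the second case, make these assumptions, none of which comes from the documents:

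- An unlisted event has the same true 12-week risk p in all arms, with onset spread evenly over the 12 weeks.
- The calls elicit every such event with onset up to week 8.
- Any other such event is recorded with probability v in either group.

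Share recorded in the active arms: 8/12 + (4/12)·v. Share recorded in the control arm: v. The expected apparent relative risk is the ratio of the shares, and p cancels:

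(2/3 + v/3) / v

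- v = 1: 1.00 / 1.00 = 1.0
- v = 0.5: 0.833 / 0.50 = 1.67
- v = 0.25: 0.75 / 0.25 = 3.0

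At p = 10% and v = 0.5, the expected recorded events are 30 × 0.10 × 0.833 = 2.5 in the active arms and 15 × 0.10 × 0.5 = 0.75 in control, that is 8.3% against 5.0%. If the calls in practice elicit no more than would be reported anyway, the ratio stays at 1.

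**The case against.** The strongest reply is that this is an argument from silence. The article condenses a full protocol, and the case report form, call script and questionnaire are not shown. Naming symptoms to be asked about does not say that nothing else is asked, and Table 1 gives two sources for ARs. The form may already hold an open line. A fixed list is also a legitimate way to obtain comparable data, and the products are described as commercially available foods of minimal risk. All of this lowers the weight of the point. It does not remove it, because the article does state the week-12 method and the calls, and as stated they differ by arm.

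A reader might go further and infer that any reaction outside the list comes to light only if a participant volunteers it. The documents do not support that. The sentence after the list schedules AR calls by the coordinator for the intervention group, with no symptom list attached. The IBS-SI asks about abdominal pain and distension, both off the list. Serious illness with a possible causal link goes to the Efficacy and Safety Committee whatever its type. For the same reason, a calculation of how often a reaction would be missed among the 30 treated participants by volunteering alone would describe a procedure that the plan does not use.

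These routes leave the gap in place. The calls are not described for controls and end at week 8. The IBS-SI gives a score without onset, treatment need or prognosis. The Committee deals with serious illness only.

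**Conclusion.** The point holds as a minor weakness in harms ascertainment. As described, the one AR enquiry common to all arms is limited to five symptoms, while the less restricted enquiry reaches the active arms only and stops at week 8. Unlisted reactions may therefore be under-recorded late in the study and unevenly recorded between arms. The likely direction is more recorded events in the active arms, if call-elicited events enter the comparison.

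The size cannot be taken from the documents. The ratios of 1.0, 1.67 and 3.0 show how far a true relative risk of 1 could move. They rest on assumed recording probabilities, even onset and fully effective calls, and they concern a handful of events. The conclusion also assumes that the unseen form has no open item and that controls receive no AR calls. If either assumption is wrong, the point shrinks or disappears. The primary outcome, its analysis and the sample size are unaffected.

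**What to change.** Add one open question to the week-12 questionnaire in all three arms, asking about any other new or worse health problem since allocation. It should not ask for attribution to a product, since controls take none. Attach the same follow-up on onset, severity, treatment and prognosis as for the listed symptoms. If the form already has such an item, say so in section 2.12.

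Report listed and unlisted events separately by arm. Base the between-arm AR comparison in section 2.14 on this common week-12 enquiry, and describe events learned from the week-4 and week-8 calls separately for the active arms.

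The cost is one line on an existing form and a little coding of free text. Some unrelated minor complaints will be recorded, and the control arm shows their background rate. Nothing else in the design changes.
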